### 1.3. Conceptual framework

[figure not shown]

**Figure 1 Conceptual framework Modified from 2002 WHO Risk factor model for promotion of oral health (Petersen, P.E., 2005)**

Adolescent's demographics (age and sex) and parental/guardians (education and SES) affect oral health related-behaviors and oral health. Application of a 6 months modified BPOC will lead to an improvement in oral health-related behaviors such as brushing teeth two times a day, use of fluoridated tooth paste, reduced risky sugar consumption and dental checkups at least once a year. Improved health-related behaviors will ultimately lead to improvement in adolescent's oral hygiene and health status. Improvement in adolescent's oral hygiene and health status ultimately lead to reduced impacts in oral health-related quality of life among adolescents. The intervention can also directly improve adolescent's oral hygiene and health status and reduce impacts on adolescents OHRQoL.

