### **2.2. Specific Objectives**

- 1 To determine prevalence and distribution of dental caries, periodontal conditions and oral impacts on daily performance among adolescents in Copperbelt Province, Zambia
- 2 To determine the association between dental caries and oral health related quality of life among adolescents in Copperbelt Province
- 3 To assess the effects of a six months modified basic package of oral care intervention on knowledge and behaviors related to dental caries after 18 and 24 months of follow up.
- 4 To assess the effects of a six months modified basic package of oral care intervention on prevalence of dental caries after 18 and 24 months of follow up
- 5 To assess the effects of a six months modified basic package of oral care intervention on prevalence of oral impacts on daily performance after 18 and 24 months of follow up

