#### **4.6. The trial intervention**

The trial intervention is a modified WHO –BPOC which include all the 3 packages of BPOC plus oral health education. The first package, Oral Urgent Treatment (OUT) will include simple extraction of teeth beyond restorable condition and referral for teeth requiring clinic set up for removal. The second package which is Atraumatic Restorative Treatment (ART) will be executed using hand instruments only by removing decayed part of teeth with cavities not reaching the pulp or not diagnosed as irreversible pulpitis then filling with Fuji IX Glass- ionomer. The third component (Affordable Fluoridated Tooth pastes) will be done by providing 250g pack of fluoride toothpaste every two months and toothbrushes every three months for 18 months. In addition to WHO-BPOC the study will also give peer provided oral health education. The peer educators will be furnished with the following printed messages to deliver to their classmates in the intervention groups once after every two weeks for a period of 18 months;

1. Restrict the frequency of taking sugary food and drinks in the diet to less than five times per day.
2. Brush your teeth for 2 minutes ensuring all the surfaces are cleaned; twice per day in the morning and evening before retiring to bed.
3. Use fluoride toothpaste to brush, spit the foam but do not rinse it out.
4. Change your toothbrush every 3 months or when bristles flare out.
5. Advise your parent or guardian to buy a tooth paste containing at least 1450 ppm fluoride and to take you for dental check up at least once a year.

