**Table 1 Summary of intervention set up**

| Baseline
data
collection                                                                                                            | Randomization | Activities in each group                       | Activity Schedule                                |                 |                 |                 |                 |                 |                 |                 |                 |         |                  |
|-------------------------------------------------------------------------------------------------------------------------------------------|---------------|------------------------------------------------|--------------------------------------------------|-----------------|-----------------|-----------------|-----------------|-----------------|-----------------|-----------------|-----------------|---------|------------------|
|                                                                                                                                           |               |                                                | Months                                           |                 |                 |                 |                 |                 |                 |                 |                 |         |                  |
|                                                                                                                                           |               |                                                | 1-2                                              | 3-4             | 5-6             | 7-8             | 9-10            | 11-12           | 13-14           | 15-16           | 17-18           | 19-24   |                  |
| 

• OHK

• OHRB

• Plaque

• Gingival bleeding

• Dental caries

 | Intervention  | 1. Peer led OHE                                | OHE once after every 2 weeks (total 36 sessions) |                 |                 |                 |                 |                 |                 |                 |                 | -No OHE |                  |

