|                                                                                                                                           |               | 2. OUT sessions 1-3                            | 1 st                                  |                 |                 |                 |                 | 2 nd |                 |                 | 3 rd | No OUT  |                  |
|                                                                                                                                           |               | 3. ART sessions 1-3                            | 1 st                                  |                 |                 |                 |                 | 2 nd |                 |                 | 3 rd | NO ART  |                  |
|                                                                                                                                           |               | 4. AFT sessions 1-9                            | 1 st                                  | 2 nd | 3 rd | 4 th | 5 th | 6 th | 7 th | 8 th | 9 th | -No AFT |                  |
|                                                                                                                                           |               | 5. Follow ups (at 3, 6, 12, 18, and 24 months) |                                                  |                 | 1 st |                 |                 | 2 nd |                 |                 | 3 rd |         | 4 th  |
|                                                                                                                                           | Control       | 1. Modified BPOC (OHE/OUT/ART/AFT) at the end  |                                                  |                 |                 |                 |                 |                 |                 |                 |                 |         | B
P
O
C |

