#### **4.6.2. Intervention period**

The intervention will be instituted immediately after base line data collection and randomization and will be for a period of 24 months follow up.

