## Appendix 6- Analysis Plan by objectives

| No | Objective                                                                                                                                                                       | Analysis                                                                   | To be reported as                                              |
|----|---------------------------------------------------------------------------------------------------------------------------------------------------------------------------------|----------------------------------------------------------------------------|----------------------------------------------------------------|
| 1  | To determine prevalence and distribution of dental caries, periodontal conditions and oral impacts on daily performance among adolescents in Copperbelt Province, Zambia        | Frequency distribution, chi-square test, logistic regression               | Number and percentage, odds ratio with 95% confidence interval |
| 2  | To determine the association between dental caries and oral health related quality of life among adolescents in Copperbelt Province                                             | Frequency distribution, chi-square test, hierarchical logistic regression  | Number and percentage, odds ratio with 95% confidence interval |
| 3  | To assess the effects of a six months modified basic package of oral care intervention on knowledge and behaviors related to dental caries after 18 and 24 months of follow up. | Frequency distribution, chi-square test, generalized estimating estimation | Number and percentage, odds ratio with 95% confidence interval |
| 4  | To assess the effects of a six months modified basic package of oral care intervention on prevalence of dental caries after 6 and 12 months of follow up                        | Frequency distribution, chi-square test, generalized estimating estimation | Number and percentage, odds ratio with 95% confidence interval |
| 5  | To assess the effects of a six months modified basic package of oral care intervention on prevalence of oral impacts on daily performance after 18 and 24 months of follow up   | Frequency distribution, chi-square test, generalized estimating estimation | Number and percentage, odds ratio with 95% confidence interval |

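### Appendix 6 sets the caries objective, a primary outcome, at 6 and 12 months, whereas section 2.2 sets it at 18 and 24 months

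*Protocol*

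**What the plan says.** **Visits for caries.** Objective 4 in section 2.2 concerns "prevalence of dental caries after 18 and 24 months of follow up". Section 4.12 says that the analysis plan per objective is summarised in Appendix 6. Row 4 there gives the same objective as "prevalence of dental caries after 6 and 12 months of follow up". Rows 3 and 5, for knowledge and behaviours and for oral impacts, keep 18 and 24 months as in section 2.2. The analysis and reporting cells of row 4 match those of rows 3 and 5 and name no visit. Section 4.10 lists dental caries status among the primary outcomes. Section 4.9.1 schedules follow-ups at 6, 12, 18 and 24 months and has each variable analysed at baseline and at every follow-up.

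**Length of the intervention.** Objectives 3 to 5 refer to a "six months modified basic package of oral care intervention", and Appendix 6 rows 3 to 5 repeat that label. Section 1.3 says "Application of a 6 months modified BPOC will lead to an improvement in oral health-related behaviors". Section 4.6 has the peer education given "once after every two weeks for a period of 18 months" and supplies toothpaste and brushes over the same 18 months. Table 1 lists "AFT sessions 1-9", one per two-month column up to months 17-18, with no delivery to the intervention arm in months 19-24. Section 4.14 has the interventions stop six months before the last follow-up.

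**The concern.** One primary-outcome objective carries two different pairs of visits in current text. Months 6 and 12 are real scheduled visits, so row 4 reads as a workable instruction, and an analyst following the appendix would not see it as impossible. That analyst would answer Objective 4 with data taken while the package was still being delivered. Section 2.2 intends the end of delivery and a point six months after it. Those are different questions: the effect part-way through the package, against the effect of the completed package and whether it lasts. With both pairs on paper, the protocol also gives no firm ground for holding a report to one of them.

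The six-month label adds a smaller difficulty. It misdescribes the intervention under test in the objectives themselves.

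**Working it through.** **1. Visits, side by side.**

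| Objective | Section 2.2 | Appendix 6 |
|---|---|---|
| 3, knowledge and behaviours | 18, 24 | 18, 24 |
| 4, dental caries | 18, 24 | 6, 12 |
| 5, oral impacts | 18, 24 | 18, 24 |

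For Objective 4 the sets {18, 24} and {6, 12} have no visit in common.

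**2. Length of delivery, from the plan's own counts.**
- Toothpaste (Table 1): 9 rounds × 2 months = 18 months.
- Education (Table 1): 36 sessions ÷ 2 per month = 18 months. Counted strictly every 14 days, 18 × 30.4375 ÷ 14 ≈ 39 sessions, so the stated 36 rests on two sessions a month.
- Section 4.14: last follow-up at 24 months − 6 months = month 18.

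All three agree with section 4.6. A six-month package would have 6 ÷ 2 = 3 toothpaste rounds and 6 × 2 = 12 education sessions (about 13 at strict 14-day spacing), not 9 and 36.

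**3. Where each visit falls against an 18-month delivery.**
- Month 6: 18 − 6 = 12 months before the end.
- Month 12: 18 − 12 = 6 months before the end.
- Month 18: at the end.
- Month 24: 24 − 18 = 6 months after the end.

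**4. Amount delivered by the row 4 visits.** Table 1 places the extraction and restoration sessions in months 1-2, 11-12 and 17-18.

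| Component | By month 6, at most | By month 12, at most |
|---|---|---|
| Education | 12 of 36 | 24 of 36 |
| Toothpaste rounds | 3 of 9 | 6 of 9 |
| Extraction and restoration sessions | 1 of 3 | 2 of 3 |

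These fractions describe how much had been delivered. They do not measure bias.

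**5. Count of the six-month label.** Objectives 3 to 5 (3) + Appendix 6 rows 3 to 5 (3) + section 1.3 (1) = 7. Six are spelled out, and the one in section 1.3 uses a numeral.

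**6. Sample size.** The calculation in section 4.4 reproduces: 4(1.96 + 1.03)² × 1.34² ÷ 0.268² = 894.01; 894 × 1.79 = 1600.26; 1600 × 1.10 = 1760. No visit month enters it, so it does not depend on this point.

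**The case against.** The strongest reply is that row 4 is a copying slip. Section 2.2 is where objectives are set, Appendix 6 only summarises their analysis, and rows 3 and 5 show the intended pattern. The analysis cell of row 4 differs in nothing, and section 4.9.1 has every follow-up analysed anyway. Most of this stands. It shows which pair was probably meant and keeps the consequence narrow. It does not remove the contradiction for a primary outcome, in the table to which section 4.12 sends the analyst.

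Several stronger readings are tempting but not supported:

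- **That caries at 18 and 24 months goes unanalysed.** Section 4.9.1 covers all four follow-ups.
- **That row 4 makes sense only for a six-month package, so that visits and label must be corrected together.** Months 6 and 12 are legitimate interim visits within an 18-month package. Correcting row 4 alone removes the conflict with Objective 4.
- **That the earlier pair suits caries least, because section 4.14 calls even 24 months too short.** That limitation concerns caries increment, while Objective 4 concerns prevalence. The same section offers the staged caries index and follow-up beyond 24 months as mitigation.
- **That seven labels are seven separate errors.** They are one drafting phrase repeated, and the delivery text is consistent at 18 months.
- **That section 4.6.2 sets a rival duration.** Its phrase "will be for a period of 24 months follow up" can be read as the length of follow-up.

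**Conclusion.** The point holds as an internal contradiction that should be fixed. Appendix 6 row 4 names visits for a primary-outcome objective that share none with section 2.2. Taken as written, it would answer Objective 4 at 12 and 6 months before the end of delivery instead of at 0 and 6 months after it. This rests on the 18-month delivery, which section 4.6, Table 1 and section 4.14 support independently of one another. The mislabelled duration is real but secondary.

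The size is limited: no visit is lost and no sample size or power figure changes. The protocol gives nothing from which to estimate an effect on the caries result, so no bias is claimed.

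**What to change.** In Appendix 6 row 4, change the visits to 18 and 24 months, and state that these two visits answer Objective 4 while caries results at 6 and 12 months are interim.

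As a secondary correction, replace the six-month label with 18 months in Objectives 3 to 5, Appendix 6 rows 3 to 5 and section 1.3, so that the objectives describe the intervention actually delivered. Tidying section 4.6.2 is optional.

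The cost is wording only: one cell with its clarifying statement, and seven labels. All four follow-ups are already scheduled, so no extra visit, data collection or recruitment is needed.
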